### Intervention delivery

As stated earlier, face-to-face delivery is not always an optimal method for disseminating evidenced based psychological interventions in SMEs. CBT interventions in organizational settings are typically delivered to small groups of people which are difficult for SME employees to access. Men are particularly hard to reach in this manner with high rates of refusal by men (50–70%) to attend groups administered by mental health services. Face-to-face interventions are also costly to provide; typically involving high salary costs for the specialized delivery. In addition, people living in remote or rural areas are also disadvantaged as services providing specialized programs often do not include remote areas [26]. Thus, there is an urgent need to identify methods to improve the transportability of occupational health programs [27]. As cost-effective interventions are obviously important to increasing service delivery in workplace mental health promotion, a self-administered treatment (SAT) or self-help modality will be developed and tested in this research. SAT versions of CBT usually involve a combination of video material, self-guided workbooks, and telephone support. SATs can reach large numbers of people, are more acceptable to those who would prefer to address emotional issues in the privacy of their own homes and have demonstrated efficacy in reducing levels of psychosocial distress and health-related risk factors in both clinical and non-clinical populations [27,28].

However, there are a number of important empirical questions that need to be answered to facilitate the optimal delivery of self-help programs in the workplace. First, obtaining high levels of employee engagement with workplace mental health programs has been difficult, particularly among men due to mental health stigma. Our research offers an SAT modality in order to overcome this problem but also includes an empirical evaluation of the predictors of treatment credibility, satisfaction and compliance.

Second, contradictory evidence exists concerning the efficacy of a telephone facilitator for boosting the potential treatment power of an SAT [29]. Whilst it might be expected that a telephone facilitated intervention group will show significantly greater impact on outcomes; an effect mediated by greater intervention engagement and adherence; this component increases the cost of delivery substantially and needs to demonstrate a strong economic case to be funded in future trials. This research will formally evaluate the return on investment for two intervention formats (with and without telephone support).

Finally, whether self-help programs should target those with existing problems or symptoms, or else be delivered universally is also uncertain. A recent meta-analysis of self-help programs for depression [30] found that effect sizes were larger in targeted or 'indicated' programs that focus on people with existing depressive symptoms. In contrast, other researchers report that self-help programs are more effective in improving adjustment in individuals with less severe problems [27]. SATs have been found to be particularly useful in the initial or mild stages of mental disorders as they act as a gateway to further therapy for individuals who are hesitant about receiving treatment [31]. This research will investigate the specific mechanisms of intervention effects in order to answer these questions [32].

### Self-administered intervention group

This group will receive a package containing the '*Business in Mind*' DVD program (60 minutes) and accompanying guidebook with instructions about how to progress through the program activities.

### Telephone-facilitated intervention group

In addition to the '*Business in Mind*' program materials, participants in the facilitated condition will also receive six, thirty-minute telephone calls, over a three month period. The telephone calls aim to review tasks and content presented in the DVD, and to address any concerns or difficulties participants encounter engaging with and carrying out the related activities. The process will be guided by a protocol which prompts recall, reviews guidebook tasks, and provides encouragement and assistance. The first call will occur in week one in order to provide an overview of the program, develop some rapport between the participant and facilitator and prompt initial engagement with the intervention materials. Calls two to five occur on a fortnightly basis and are targeted at modules 1–4 of the DVD. In the final telephone call, managers are encouraged to explore ways of generalizing their skills and continuing their personal development.

### Control group

An active control condition consisting of minimal psychoeducation related to depression and the workplace will be employed. The content of this 15 minute DVD and resource folder will be adapted from material delivered in *beyondblue's *workplace training program. This material provides information that helps managers to identify common symptoms of depression in themselves or those under their supervision, and promotes the importance of help-seeking and early intervention. As an active control condition, the content is instructional in relation to mental health literacy and is presented in multimedia format, but does not include any therapeutic/psychological development content.

### Outcome Assessment

A number of measures will be used to assess intervention processes and outcomes.

*Mental health *(employees/managers): Mental health symptoms will be assessed with the K-10 depression/anxiety screening instrument [33].

*Work outcomes *(employees/managers): This will include job satisfaction [34], job Tension [35] and self-reported lost productivity from absenteeism and presenteeism [4].

*Direct effect of intervention *(managers only): The primary outcomes for intervention participants are the Psychological Capital Inventory [24] and the Cybernetic Coping Scale [36]. We will also use a life events scale [37] to examine the protective effects of any psychological capital improvement and the SF-12 as a general indicator of self reported health [38].

*Psychosocial work environment *(employees only): Employees will be asked to report their perceptions of team affective climate [39], relational justice [40], and supervisor support [41].

*Control variables *(employees/managers): the Core-Self Evaluation Scale which measures the emotional stability personality trait [42]; participants will also be asked about any medical or psychological treatment begun or discontinued during the period since the last survey.

*Intervention satisfaction *(managers only): Intervention participants will be asked to report intervention engagement, compliance, credibility [26].

*Psychoeducation effectiveness *(employees/managers):Managers will be asked about their understanding of mental health conditions, attitudes toward depressed employees, their confidence in discussing mental health issues, and help-seeking intentions [13]. Employee perceptions of mental health climate will be assessed by asking participants about their level of confidence in communicating with managers about mental health concerns and the presence of mental health information in their workplace [43].

Demographic data and business descriptors will also be collected.

### Qualitative assessment

In order to gather additional information relevant to understanding intervention processes and effects, telephone interviews will be conducted with participants who volunteer for a follow-up interview 2–4 weeks after the post-intervention survey (both employees and managers). These interviews will assist in understanding participants experiences of the intervention and in dissemination of the intervention beyond the trial setting.

### Treatment adherence and integrity

A process evaluation framework will be employed to test the extent to which the interventions are successfully implemented (i.e. dose delivered, dose received, and fidelity; [44]). The telephone facilitator will self-rate adherence to protocols in delivery as well as their counseling competency skills using validated clinical instruments. All telephone sessions will be audio-taped (subject to participant consent) and rated by the third author in supervision sessions. In addition, two independent experts will rate 10% of randomly selected sessions for treatment fidelity and competence.

### Data analysis

The primary data analysis will compare the efficacy of the two intervention treatment conditions in comparison to the active control group, based on differences in manager's mental health, psychological capital, and work outcomes. Evaluation will be based on an intent-to-treat analysis. A generalised estimating equations approach using the SAS statistical package will be employed. This approach enables the inclusion of all available data including participants who are lost to follow-up or who have incomplete data. Secondary data analyses will test for differences across the groups in employee mental health and perception of the psychosocial work environment, with adjustment for clustering if necessary. Reasons for treatment success/failure will be identified also via a process evaluation framework. An economic evaluation will estimate the incremental cost-effectiveness of the two intervention treatment conditions in comparison to the active control, from both a societal and employer perspective to ensure direct relevance to the SME context. Indirect costs will include lost productive time from absenteeism and presenteeism. Economic analysis will be informed by another of our studies currently underway which is estimating the societal and employer costs associated with depression in the Australian workforce [3].

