### Recruitment of participants

We aim to recruit a minimum of 249 managers within SMEs throughout one state of Australia (Tasmania). Managers will primarily be drawn from the networks of three partner organizations collaborating with this research (*beyondblue *– the Australian national depression initiative, Workcover – a statutory occupational health and safety body and the Chamber of Commerce and Industry – a local business association). A mailing list of approximately 1250 managers of SMEs has been compiled from these networks. Cross-sectional self-report surveys of managers obtain an average response rate of 30% [20]. However, given the longitudinal and intervention requirements of this research it is conservatively estimated that 20% of the 1250 managers invited will participate (N = 250 at baseline). Adjusting for attrition we anticipate a sample size of N = 200 at post intervention assessment. Employing Cohen's (1992) formula, a 3 group ANOVA with an effect size of 0.5 would provide a power of 0.8 (*a *= 0.05) with 156 participants (52 per group). We based our anticipated effect size of 0.5 on two meta-analyses [21,22].

Information about the study will also be provided in the media and via local small business associations and potential participants will be invited to contact the research team for more information about the study. To be included, participants must have a managerial role within a business employing less than 200 employees, be over 18 years of age and have access to a telephone and computer/DVD player.

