Low participation and/or high drop out rates are often a problem in mental health promotion intervention trials. In an attempt to increase response rate and reduce attrition we have ensured our intervention materials are highly relevant to the business environment and a persuasive rationale for the importance of psychological wellbeing of managers and staff to the bottom line is provided in the recruitment materials. We have also included incentives for continued participation which may help in retaining a reasonable proportion of our control group.

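### Including all available data in a GEE does not by itself protect the manager comparison from dropout bias; a baseline-adjusted method valid under missing at random should be fixed, with one sensitivity analysis

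*Protocol article*

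**What the plan says.** The Data analysis section sets the target: "The primary data analysis will compare the efficacy of the two intervention treatment conditions in comparison to the active control group". The principle is intent-to-treat ("Evaluation will be based on an intent-to-treat analysis") and the method is GEE: "A generalised estimating equations approach using the SAS statistical package will be employed". The only reason given that bears on dropout is that "This approach enables the inclusion of all available data including participants who are lost to follow-up or who have incomplete data". The section names no missingness assumption, working correlation, weighting, imputation or baseline adjustment.

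The article expects losses. The Abstract allows for 20% attrition, and Recruitment of participants states: "Adjusting for attrition we anticipate a sample size of N = 200 at post intervention assessment". Under Study Design, the comparison with control runs to a further survey at 6 months. Strengths and limitations adds that "Low participation and/or high drop out rates are often a problem in mental health promotion intervention trials" and hopes that incentives will help to keep control-group managers in the study. Contact differs by arm: six thirty-minute calls, a DVD package without calls, or a 15-minute DVD with a resource folder.

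**The concern.** Keeping every available record in the model settles who is analysed. It does not settle whether the estimate is valid. Unweighted GEE solves its estimating equations on the observed records. Those equations are assured to have mean zero at the true effect only if dropout is unrelated to the outcomes, given the covariates in the mean model. If managers leave because of how they scored earlier, and that relation differs between arms, the observed arm means drift apart for reasons other than treatment. The estimate can then be too small or too large, depending on who leaves.

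Likelihood-based models for continuous scales use the earlier scores of those who leave and are valid under the weaker condition of missing at random. They are available in the SAS package already named. At stake is the accuracy of the manager comparison at post-intervention and 6 months. A separate matter is precision: baseline scores are collected, and using them as a covariate would add power under either method.

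**Working it through.** **Inputs from the article.** 83 managers per arm, 20% attrition, effect size 0.5, power 0.8, alpha 0.05, and surveys at baseline, post-intervention and 6 months.

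**The plan's own figure.** The article states that "a 3 group ANOVA with an effect size of 0.5 would provide a power of 0.8" with 52 per group. In a noncentral F calculation for three groups with f = 0.25 (0.5 read as a standardised difference of medium size), 52 per group gives power 0.797, and 53 are needed for 0.80. The figure is reproduced. Attrition: 83 × 0.8 = 66.4 per arm, and 250 × 0.8 = 200. The sample size is not at fault on this point.

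**Bias, set-up A (assumptions).** Simulation with 60,000 per arm, true effect 0.5 SD, correlation 0.6 between visits, and logistic dropout with slope 1 per SD. Bias at 6 months, in SD:

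| Dropout depends on | Loss | Independence GEE | Independence GEE + baseline covariate | Exchangeable GEE | Unstructured GEE | Baseline-adjusted likelihood |
|---|---|---|---|---|---|---|
| Post score, same in both arms | 20% / 35% | about 0 | about 0 | about 0 | about 0 | about 0 |
| Post score, control only | 20% | -0.11 | -0.05 | -0.01 | -0.01 | -0.01 |
| Post score, control only | 35% | -0.19 | -0.08 | -0.01 | -0.02 | -0.01 |
| Post score, opposite directions | 20% | -0.21 | -0.08 | 0.00 | -0.01 | 0.00 |
| Post score, opposite directions | 35% | -0.35 | -0.15 | -0.01 | -0.03 | 0.00 |
| Unobserved 6-month score, control only | 20% | -0.17 | -0.12 | -0.11 | -0.11 | -0.12 |
| Unobserved 6-month score, control only | 35% | -0.29 | -0.19 | -0.19 | -0.19 | -0.19 |

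Values of about 0.01 are simulation error. Completely random dropout gave about 0 for every method. Dropout that depends on baseline in the control arm only gave -0.10 (20%) and -0.18 (35%) for independence GEE, and about 0 once baseline was a covariate. At 20% loss, the score-dependent rows are 0.11/0.5 = 22% and 0.21/0.5 = 42% of the design effect.

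**Bias, set-up B (assumptions).** Correlations 0.6/0.55/0.65, dropout slope 0.7 in control and 0 or -0.7 in intervention, 20% lost at post and about 32% by 6 months. Estimates of the true 0.50 at post / 6 months:

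- Independence GEE: 0.42 / 0.37 (control only) and 0.34 / 0.23 (opposite directions).
- Unstructured GEE: 0.496 / 0.497 and 0.494 / 0.489.
- Unstructured maximum likelihood: 0.494 / 0.488 and 0.499 / 0.486.
- Equal slopes of 0.7 in both arms: even independence GEE gives 0.50 / 0.50.
- With a clearly non-exchangeable truth (0.7/0.45/0.7), exchangeable GEE gives 0.491 / 0.518 and 0.479 / 0.528, within 0.03 SD.

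**Power from baseline adjustment.** For one pairwise comparison at 66 per arm and d = 0.5, two-sided alpha 0.05:

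- Post score alone: 0.5 × √(66/2) = 2.872; 2.872 - 1.960 = 0.912; power 0.819 (0.814 with the t distribution).
- Adjusted for baseline with correlation ρ, the residual variance is multiplied by 1 - ρ², so 2.872 is divided by √(1 - ρ²).
- ρ = 0.3: 3.011, power 0.853. ρ = 0.5: 3.317, power 0.913. ρ = 0.6: 3.590, power 0.948. ρ = 0.7: 4.022, power 0.980.
- Effect detectable with 80% power: (1.960 + 0.842) × √(2/66) = 0.49 SD unadjusted, falling to 0.47, 0.42, 0.39 and 0.35 SD.

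The article gives no baseline-outcome correlation, so ρ is an assumption.

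**The case against.** The strongest reply is that the article says only that GEE will be used. It does not exclude weighting, imputation, a baseline covariate or a sensible working correlation, and a condensed article may leave these to the analysis plan. It claims that data are included, not that the result is unbiased. All of this stands, so the silence on these details is not itself the fault. What remains is that the one stated answer to dropout does not deliver the protection needed.

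A reader might infer that GEE as planned would lose a fifth to two fifths of the effect. The article does not support that. The large figures need an independence working correlation, which it does not specify, and score-dependent dropout that differs by arm, which it does not describe. Its remark on keeping the control group suggests at most a different rate of loss, and a different rate alone does not bias the contrast. The opposite-directions scenario has no support in the text. With an exchangeable or unstructured working correlation, GEE and likelihood performed almost alike here.

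Two further inferences go too far. A likelihood model does not cure dropout in general: when loss depends on unobserved scores it carries the same bias as GEE with a baseline covariate. Nor does leaving GEE add power: the gain comes from the baseline covariate and is the same within GEE.

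**Conclusion.** The point holds in a limited form. Inclusion of all available data is not an adequate safeguard against dropout, because unweighted GEE is assured valid only when dropout is completely at random or explained by covariates in the mean model. The possible size is roughly 0.1 to 0.2 SD on a 0.5 SD effect at about 20% loss, and up to 0.35 SD at 35%. This is conditional on an independence working correlation and on score-dependent dropout that differs by arm. It is close to zero if either condition fails, provided that dropout depends only on observed scores. If dropout depends on unobserved scores, bias of about 0.12 SD (20% loss) to 0.19 SD (35%) remains under a baseline-adjusted likelihood model as well. The dropout slopes, correlations and 6-month loss are illustrative assumptions. The power gain (about 0.81 to between 0.85 and 0.98) rests on assumed correlations of 0.3 to 0.7.

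**What to change.** State the missingness assumption and choose one of two routes for the continuous manager outcomes:

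- **Likelihood route.** A repeated-measures model with arm by visit and unstructured covariance. Either adjust for the baseline score or constrain the arms to a common baseline mean. The constrained form keeps managers with only a baseline survey in the model; with baseline as a plain covariate they add no information on the effect.
- **GEE route.** Specify a working correlation other than independence, include the baseline score as a covariate, and add inverse-probability weighting or multiple imputation that uses earlier scores and arm.

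Under either route, add one sensitivity analysis in which dropout is not at random, for example with unobserved scores shifted over a stated range by arm.

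The cost is small: a few sentences, a different or extended SAS procedure and a little more analysis work, with no new data, visits or participants. The likelihood route assumes approximate normality of the scale scores.

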## Methods/Design

### Study Design

The research design employed a three arm randomized controlled trial including 249 managers (83/83/83 – see power calculations below). The trial is also evaluated using a sample of employees of each of these managers (estimated to be approximately 2490 employees). Measurements are scheduled at baseline, directly after completion of the intervention, and at 6 months follow up. After this time the managers in the control group will be offered the intervention on a self administered basis (see intervention delivery below). Longer-term follow up measures at 12 and 24 months post intervention will examine changes in managers' risk for depression and the potential for the intervention to protect or 'inoculate' them during significant work or life challenges. Figure 2 presents the flow chart representing the study design.

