## Discussion

### Strengths and limitations

The intervention we have developed is based on the integration of a number of evidence based approaches for mental health promotion. To the best of our knowledge, this will be the first RCT of a multilevel mental health promotion intervention that specifically targets SME managers and employees with a unique psychological capital-emotional contagion theoretical mechanism. By integrating current knowledge in clinical and organizational psychology with a public health perspective, the study has also incorporated a number of innovative and significant objectives. First, in addition to directly examining the efficacy of our intervention for improving the mental health of managers, we also aim to further identify the processes by which the psychological state of managers affects their subordinate's well-being via the workplace psychosocial environment. Second, by investigating a range of cost indicators such as absenteeism and presenteeism, we will estimate the economic value of this intervention. Thirdly, we aim to investigate the impact of different intervention formats, the specific problems they address and the characteristics of the participants who respond to them and find them helpful. Each of the objectives will directly inform policy and decision-making by our research partners, business stakeholders and government bodies. It should also be noted that the study protocol was approved by the Human Research Ethics Committee (TAS), which is a joint agreement between the University of Tasmania and the Department of Health and Human Services (DHHS). Funding of the trial, obtained from the Australian Research Council, was awarded via a process of competitive, systematic peer review.

A limitation of this trial is that only people with a computer or DVD player can be included. However, it is estimated that in 2007, 73% of Australian households had a computer and 89% had a DVD player . Whilst ensuring high external validity of our sample, the leniency of the inclusion criteria is also a potential limitation of the study. Not excluding participants previously or currently being treated for mental disorder may be a potential confounder of our results. However, measurement of this status at baseline and throughout the study will allow us to take this into account.

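### The analysis section sets both formats against the active control and names no telephone versus self-administered contrast, although the telephone component is meant to make its own economic case

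*Protocol article*

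**What the plan says.** **The question.** Under Intervention delivery, the protocol article says of telephone support that "this component increases the cost of delivery substantially and needs to demonstrate a strong economic case to be funded in future trials". It then commits the trial: "This research will formally evaluate the return on investment for two intervention formats (with and without telephone support". The same paragraph raises, as something that might be expected, that "a telephone facilitated intervention group will show significantly greater impact on outcomes", after noting that the evidence on this is contradictory. Strengths and limitations lists as the third objective that "we aim to investigate the impact of different intervention formats".

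**The planned comparisons.** Under Data analysis, for manager outcomes: "The primary data analysis will compare the efficacy of the two intervention treatment conditions in comparison to the active control group". For the economics: "An economic evaluation will estimate the incremental cost-effectiveness of the two intervention treatment conditions in comparison to the active control". The one analysis described as running across the groups concerns employees: "Secondary data analyses will test for differences across the groups in employee mental health and perception of the psychosocial work environment".

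**The design.** Study Design describes a "three arm randomized controlled trial including 249 managers (83/83/83" split, so both formats and the control are randomised side by side. No section names a telephone versus self-administered contrast on manager outcomes, costs or cost-effectiveness.

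**The concern.** The two intervention arms share the DVD and guidebook and differ by the six telephone calls. An economic case for the calls is therefore a case about the difference between those two arms. The article states a comparator for its economic and efficacy analyses, and that comparator does not isolate this difference. This is a mismatch between a stated question and a stated analysis, not a detail that the article leaves open.

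Two things are at stake. On cost-effectiveness, the telephone format's ratio against control mixes the return on the DVD with the return on the calls, so a funder could accept or reject the calls on a figure that does not describe them. On effects, one format reaching significance against control and the other not would be no test of a difference between them.

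The later visits sharpen the point. According to the Abstract, only the intervention groups are assessed at 12 and 24 months. The comparison between formats is then the only randomised one available, and the analysis section does not name it.

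**Working it through.** **1. The plan's own sample size.** Recruitment of participants gives 52 per group (156 in total) for a three-group ANOVA with effect size 0.5, power 0.8 and alpha 0.05. Reading 0.5 as d and converting to f = d/2 = 0.25, the noncentral F gives power 0.797 at 52 per group (53 per group for a full 80%), so the figure reproduces. Reading 0.5 as f would need only 14 per group and does not reproduce it. After 20% attrition, 83 × 0.8 = 66.4 per arm and 249 × 0.8 = 199, in line with the stated 200.

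This calculation is for the omnibus test, which can be significant when the formats do not differ. With means 0, 0.5 and 0.5 SD (control and two equal formats), f = 0.236 and omnibus power at 66 per arm is 0.85.

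**2. What each ratio measures.** Let ΔC and ΔE be a format's incremental cost and effect over control, with S for self-administered and T for telephone.

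- S versus control: ΔC_S / ΔE_S
- T versus control: ΔC_T / ΔE_T
- Adding telephone support: (ΔC_T − ΔC_S) / (ΔE_T − ΔE_S)

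If T is the more effective, the second ratio is a weighted average of the first and third, with weights ΔE_S/ΔE_T and (ΔE_T − ΔE_S)/ΔE_T. It is therefore below the third when S has the better ratio against control, and above it when S has the worse one.

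**3. Numbers.** The article gives no costs and no expected difference between formats, so every input here is assumed: ΔC_S = 100, ΔC_T = 400, effects in SD.

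| ΔE_S, ΔE_T | S vs control | T vs control | T vs S |
|---|---|---|---|
| 0.40, 0.50 | 250 | 800 | 300/0.10 = 3,000 |
| 0.40, 0.45 | 250 | 889 | 300/0.05 = 6,000 |
| 0.30, 0.50 | 333 | 800 | 300/0.20 = 1,500 |
| 0.30, 0.32 | 333 | 1,250 | 300/0.02 = 15,000 |
| 0.10, 0.50 | 1,000 | 800 | 300/0.40 = 750 |

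Check on the first row: 0.8 × 250 + 0.2 × 3,000 = 800. On the last: 0.2 × 1,000 + 0.8 × 750 = 800. The same 800 against control goes with 3,000, 1,500 or 750 for the calls.

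**4. Recovering the contrast from the two control comparisons.** Subtracting the increments (not the ratios) gives the point estimate. The uncertainty does not follow so simply, because both comparisons use the same control arm. With 66 per arm and unit SD, the direct contrast has standard error √(2/66) = 0.174. Combining the two control comparisons as if independent gives √(4/66) = 0.246, too large by a factor of √2.

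**5. Precision of the direct contrast.** For a two-group comparison, two-sided 0.05, 66 per arm, no multiplicity adjustment:

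- Detectable d at 80% power = (1.96 + 0.84) × 0.174 = 0.49.
- Power ≈ Φ(d/0.174 − 1.96): 0.21 at d = 0.2, 0.41 at 0.3, 0.63 at 0.4, 0.82 at 0.5.
- Half-width of the 95% interval = 1.96 × 0.174 = 0.34 SD.

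**The case against.** The best defence is that the article is a condensed account. It promises an evaluation with and without telephone support, its analysis paragraph excludes no contrast, and a three-group GEE model yields the pairwise comparison and its interval directly. The return-on-investment sentence, read alone, could also mean one figure per format. Dominance rules, acceptability curves and lists of secondary contrasts usually sit in a fuller plan.

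Much of this stands. A reader might infer that the plan rules out the format comparison, or that the trial cannot answer the question. The documents support neither: no sentence limits the analysis to control comparisons, and the randomised arms supply what is needed. The absence of detailed health-economic methods is no fault in an article.

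A reader might also infer that comparison with control always makes telephone support look better value than it is. That depends on the self-administered format having the better ratio against control, and the last row of the table shows the reverse. The article gives no basis for choosing a direction.

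What does not fall is the mismatch. The article names a comparator for both analyses, and it is not the one that its question about the telephone component requires. The sentence before the return-on-investment commitment asks for a case for that component. The omnibus ANOVA behind the sample size does not isolate the format difference either.

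**Conclusion.** The point holds as a mismatch between a stated question and the stated comparator, and should be corrected. The planned comparisons with control remain valid for what they estimate, but they do not give the cost-effectiveness of adding telephone support and do not test whether the formats differ.

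The size of the error cannot be known from the documents. In the assumed examples the add-on's ratio runs from slightly below the telephone ratio against control (750 against 800) to well above it (3,000 against 800, or 3.75-fold; 6,000 against 889, or 6.75-fold). These show that the ratio against control is uninformative about the add-on; they are not estimates for this trial.

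The precision figures assume 66 managers per arm at a single time point, whereas the plan uses GEE on all available data, so they are a guide only. They bear on how the contrast should be interpreted, not on whether it was planned.

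**What to change.** In the Data analysis section, alongside the comparisons with control:

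- Add the direct telephone versus self-administered contrast on the main manager outcomes, estimated from the three-arm model and reported with its confidence interval.
- Report incremental cost-effectiveness sequentially across the three arms ordered by cost, and include telephone versus self-administered with its uncertainty. Show that increment even where the self-administered format would drop out by extended dominance, as in the last row of the table, because the article's question concerns the telephone component.
- State that a non-significant difference between formats will not be read as equal effect.

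The cost is one more contrast and a reordered cost-effectiveness table, with no new data, participants or visits. The drawback is limited precision: differences much below about half a standard deviation are likely to be missed, and the interval may leave the economic case for telephone support open.
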